**Methods:**

This is a multicentre RCT. The aim is to enrol 768 patients with primary colonic cancer assigned randomly to D2 or D3 lymph node dissection. The trial is assessing the superiority of 5‐year overall survival as the primary endpoint in patients undergoing D3 lymph node dissection *versus* D2 dissection. Secondary endpoints include disease‐free survival, short‐term outcomes (30‐day morbidity and mortality), quality of complete mesocolic excision and lymph node dissection, pattern of lymph node metastasis and quality of life in patients following D2 and D3 lymph node dissection. Experience of 20 D3 and 20 D2 lymph node dissections is required for surgeons to participate in the trial. For surgical accreditation four non‐edited videos of procedures will be assessed. Patients will be followed up for 5 years after last patient enrolment. Intention‐to‐treat analysis will be performed.

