### Design

7.1

This is a randomized controlled phase III study, comparing long‐term outcomes of D2 and D3 lymph node dissections in colon cancer. Eligible patients signed written informed consent will be randomized for D2 or D3 lymph node dissection in 1 : 1 ratio.

After in‐hospital treatment postoperative recovery parameters will be evaluated, after that there will be a 5‐year follow‐up period. 768 patients will be recruited in registered centres in Saint‐Petersburg, Moscow and other centres (including other countries if any), registered for the study after patient enrolment had been commenced (up‐to‐date information about centres location can be found on https://clinicaltrials.gov/ct2/show/NCT03009227#contactlocation). Centres are activated after registration procedure (see 9·1). Patients are enrolled via screening procedure and assessing eligibility criteria. To obtain enrolment of planned number of patients additional centres will be initiated and an intensive contact with investigators in each centre will be stimulating desired enrolment.

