### Endpoints

7.3

Primary endpoint:
Overall survival (time frame: 5 years after last patient enrolment)

Secondary endpoints:
Disease‐free survival (local recurrence or distant metastases during study period)Short‐term outcomes (time frame: 30 days after operation)Lymph node metastasis pattern (number of lymph node with metastases related to number of lymph nodes studied in each lymph node group)CME quality (ratio of good, satisfactory and unsatisfactory quality)Lymph node yield (number of lymph nodes removed)Quality of life of patients

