### Follow‐up

10.6

Postoperative follow‐up includes investigations (CT chest and abdomen, colonoscopy) in 6 and 12 month, afterwards annually during the follow‐up period and examinations (or if in‐person contact is not possible it can be substituted by a phone call) in 30 days after surgery and afterwards every 3 month during follow‐up period. During follow‐up period complications, adjuvant treatment and recurrence are registered. Recurrence is registered when local recurrence or distant metastases are found during investigation (Colonoscopy, CT, MRI); serology recurrence is registered if CEA is 3 times higher than baseline. Quality of life will be assessed with validated questionnaires EORTC QLQ‐C30 and colorectal module CR 29 according to *Appendix*
S3 (supporting information).

Patients rejecting surgery after randomization or patients receiving different to randomization group treatment will be analysed in primary randomization groups. For patients rejecting treatment and follow‐up continuation of data collection without treatment is offered.

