## Sample size calculation and statistical analysis

15

To determine the sample size current data from national cancer registry was used^33^, according to which 5 year survival of colon cancer patients is 50%. Survey among surgeons revealed anticipated improvement of survival due to D3 lymph node dissection of 10%. For sample size calculation MedCalc software was used (function of sample size calculation for survival analysis (log rank test) using D. Machin method^34^), according to current survival data, sample size was determined as 762 patients. Using sample size calculation for superiority study via PASS software with C. Chow et al and J. Lachin et al method^35^, ^36^, with α – 0,05 and β – 80%, with 15% of patients lost for follow‐up in case of 3 year accrual period and 5 year follow‐up sample size was determined as 768 patients. As sample sizes obtained by different methods were similar the greater number was used to determine the sample size as 768 patients.

“Intent‐to‐treat” analysis will be performed, thus once randomized patients will be analysed in their randomization group, irrespective of actually received treatment.

For statistical analysis of primary endpoint (overall survival during the study period) Kaplan–Meier method will be implied as the probability of patients survival depends only on time after surgery, as there is no anticipated change of survival during the trial conduct. To compare survival curves long‐rank test will be used.

For secondary endpoints type of analysis will depend on the nature of data. For disease‐free survival (survival without local or distant recurrence during the study period) Kaplan–Meier curves will be used with the long‐rank test. For analysis of short‐term outcomes (morbidity and mortality), lymph node yield parametric and non‐parametric criteria will be used to compare mean values and contingency tables.

For categorical data, to assess the significance of association of two kinds of classification (contingency tables) exact Fisher's test will be implied by default as it can be used when sample distribution is only approximately equal to theoretical distribution and therefore this test is universal. For the final analysis as the sample reaches calculated size Pearson Chi square test will be used.

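### The only time origin given for overall survival is surgery, which cannot be applied to unoperated patients kept in the intention-to-treat set; two phrases also blur the end of follow-up

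*Protocol article*

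**What the plan says.** **Start of the clock.** Section 7.3 names overall survival as the primary endpoint without an origin. The only wording that bears on one is in section 15, where Kaplan–Meier is chosen because "the probability of patients survival depends only on time after surgery". The preceding paragraph of section 15 sets the intention-to-treat rule: "once randomized patients will be analysed in their randomization group, irrespective of actually received treatment". Section 10.6 extends it explicitly to the unoperated: "Patients rejecting surgery after randomization or patients receiving different to randomization group treatment will be analysed in primary randomization groups". Section 7.2 states that neither investigators nor patients are blinded and that the investigator receives the allocation by return message.

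**End of the clock.** Section 7.3 gives "Overall survival (time frame: 5 years after last patient enrolment". The registration table and the synopsis say the same, and so does the abstract: "Patients will be followed up for 5 years after last patient enrolment". Section 15 refers to the "primary endpoint (overall survival during the study period". The sample-size table, printed under section 13, has accrual 3 years and follow-up 5 years. Two phrases read differently. Section 7.1 says, following the hospital stay, "after that there will be a 5‐year follow‐up period", and the abstract describes the trial as assessing "superiority of 5‐year overall survival as the primary endpoint".

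**The concern.** A time-to-event analysis of all randomised patients needs a start date that every randomised patient has. Surgery is not such a date here. A patient who withdraws before the operation would have to be left out or given a date by some unstated rule. A patient who dies before the operation would have an event before time zero. Because allocation is known before surgery and nobody is blinded, refusals and cancellations could differ between the D2 and D3 arms. Any rule chosen later for these patients could then affect the comparison.

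At the other end, a centre that takes section 7.1 literally could stop contacting early patients at year 5, although the sample-size table counts their deaths up to year 8. The trial would then collect fewer deaths than its stated power assumes.

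**Working it through.** **Start of the clock (no arithmetic needed).**

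1. Section 15: survival time is described as time after the operation.
2. Sections 10.6 and 15: patients who reject the operation after randomisation remain in the analysis.
3. A patient in group 2 has no value for the origin in 1, and no fallback is given. The two statements cannot both be applied to that patient.
4. Scale: each 1% of randomised patients who go unoperated is 0.01 × 768 = 7.7, about 8 patients. The documents give neither a refusal rate nor an interval from randomisation to surgery, so this cannot be turned into a bias estimate.

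**End of the clock.** Inputs:

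- Section 15: control 5-year survival 50% and a 10-point gain, so h1 = −ln(0.5)/5 = 0.1386 and h2 = −ln(0.6)/5 = 0.1022. The table prints 0.139 and 0.102.
- Sample-size table: 384 per arm, loss hazard ω = 0.165 in each arm, uniform accrual R = 3, total time T = 8, alpha 0.05.

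*Reproducing the plan's figure.* With λ = h + ω, the probability of an observed death under the common cut-off is

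p = (h/λ) × [1 − (e^(−λ(T−R)) − e^(−λT)) / (λR)].

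- Control: λ = 0.3036; p = 0.4566 × [1 − (0.2191 − 0.0881)/0.9109] = 0.391; deaths 384 × 0.391 = 150.1.
- D3: λ = 0.2672; p = 0.3824 × [1 − (0.2629 − 0.1180)/0.8015] = 0.313; deaths 120.3.
- Total 270.4 (printed: 270 = 150 + 120).
- Variances h²/p: 0.0492 and 0.0333 (printed: 0.049 and 0.033).
- Power: z = 0.03646 / √[(0.0492 + 0.0333)/384] = 2.488; Φ(2.488 − 1.645) = 0.8004 (printed: 0.8004).

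The table is therefore reproduced with follow-up of 5 to 8 years per patient and a one-sided alpha of 0.05.

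*Stopping each patient at 5 years, all else unchanged.* Now p = (h/λ) × (1 − e^(−5λ)).

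- Control: 0.4566 × (1 − 0.2191) = 0.3565; 136.9 deaths.
- D3: 0.3824 × (1 − 0.2629) = 0.2819; 108.2 deaths.
- Total 245.1, about 25 fewer than planned.
- Variances 0.0539 and 0.0370; z = 0.03646 / √[(0.0539 + 0.0370)/384] = 2.369; power Φ(2.369 − 1.645) = 0.766.
- About 846 patients would be needed to restore 80%.

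Moving the origin from surgery to randomisation leaves these figures unchanged under the exponential model.

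**The case against.** The sentence in section 15 is a reason for using Kaplan–Meier, tied to the assumption that survival does not drift during the trial. It is not a formal definition of time zero. That is correct. A reader might infer that the protocol defines overall survival from surgery and will drop unoperated patients. The documents do not support this: section 10.6 says those patients are analysed as randomised and offers continued data collection without treatment. What stands is narrower. The sentence is the only origin given, and it does not fit that rule. An origin that merely went unstated could be left to the analysis plan; one that clashes with the protocol's own analysis set should be corrected.

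On the end of follow-up, a reader might infer that 5 to 8 years per patient appears only in the sample-size table. It does not. It is the formal time frame in section 7.3, the registration table and the synopsis, and it matches the abstract's follow-up sentence. Against this stand one summary clause in 7.1, which does not say that patients leave at year 5, and one label in the abstract that may be shorthand. This objection largely holds, so the end-of-clock issue is secondary.

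A reader might also conclude that the trial is underpowered. The figure of 76.6% arises only if follow-up really stops at 5 years per patient, and it uses the printed loss hazard. If 15% loss is instead assumed to be the total over 5 years (hazard 0.0325), one-sided power is 90.2% with the common cut-off and 85.7% with a fixed 5 years, both above 80%.

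**Conclusion.** The time-origin point holds: the protocol's only stated origin cannot be applied to part of its own analysis set. How much this matters depends on how many patients go unoperated, or die before surgery, in each arm. The documents give no basis for estimating that, so no bias is shown, only an avoidable opening for one.

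The end-of-follow-up point holds as an inconsistency of wording. The common cut-off governs the formal endpoint and reproduces the stated power; two phrases can be read otherwise. If that other reading were put into practice, the cost under the printed assumptions (exponential survival, loss hazard 0.165, uniform 3-year accrual, one-sided 0.05) would be about 25 deaths and 3.4 points of power (80.0% to 76.6%). If the common cut-off is followed, there is no loss.

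**What to change.** - In sections 7.3 and 15, define overall survival and disease-free survival as time from randomisation for all randomised patients, and reword the Kaplan–Meier justification to match.
- In section 7.1 and the abstract, replace the two phrases that suggest 5 years per patient with the common cut-off 5 years after the last enrolment. State that the primary log-rank test uses all follow-up to that date and that 5-year Kaplan–Meier rates are descriptive.
- If patients are in fact meant to leave follow-up at 5 years, say so and restate the power on about 245 deaths (about 76.6% under the printed assumptions).

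The cost is wording. Randomisation goes through the main centre, so the dates should already be on record. The practical burden is that early patients need status contacts beyond year 5, which the formal endpoint and the sample-size table already assume.

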### Randomization

7.2

Randomization will be performed via main centre (National Medical Research Centre of Oncology named after N.N. Petrov). Eligible patients will be randomized for D2 or D3 lymph node dissection in 1 : 1 ratio for D2 or D3 dissection according to computer generated randomization list created in beforehand^32^.

Information regarding restrictions of randomization to provide groups' homogeneity is located in the document “Mechanism of randomization in COLD trial”, kept in the main centre of the trial concealed from investigators enrolling patients.

Randomization will be performed via sending of randomization list (filled in after patient's enrolment) by electronic message to main centre, where patient will be assigned to a certain line in the randomization list. In reply message investigator receives randomization group and code of the line in the list.

There is no blinding of investigators or patients in current study.

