### Study population

8.1

The study is conducted among male and female patients older than 18 years old, who signed the informed consent form with diagnosed primary colon cancer T1‐4a N0‐2 M0‐1 (in case of resectable metastases). All patients should meet all inclusion criteria and have no exclusion criteria.

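### Section 15 names the primary log-rank test without strata; stratifying by the randomisation factors and M0/M1 would recover efficiency at almost no cost

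*Protocol article*

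**What the plan says.** - **Primary test.** Section 15 (Sample size calculation and statistical analysis) plans Kaplan-Meier curves for overall survival and adds: "To compare survival curves long‐rank test will be used" (meaning the log-rank test). It names no strata and no covariates. It does not use the word unstratified either.
- **Randomisation.** Section 7.2: "Information regarding restrictions of randomization to provide groups' homogeneity is located in the document" that the main centre keeps concealed from enrolling investigators. The article does not list the factors.
- **Population.** Section 8.1 admits patients with "diagnosed primary colon cancer T1‐4a N0‐2 M0‐1 (in case of resectable metastases". Section 8.2 requires TNM stage to be confirmed by preoperative staging, so M status and clinical T and N are known before allocation.
- **Sample size.** Section 15 assumes that "5 year survival of colon cancer patients is 50" per cent and takes an "anticipated improvement of survival due to D3 lymph node dissection of 10" per cent. The software output printed under section 13 uses one exponential hazard per arm (0.139 and 0.102, hazard ratio 0.737), a loss hazard of 0.165 in each arm, 3 years of accrual, 5 years of follow-up, alpha 0.05, 270 events and power 0.8004.

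**The concern.** The sponsor considered some factors important enough to restrict randomisation on them, but the named primary test does not use them. The population also runs from T1N0M0 to resected metastatic disease, which can differ widely in survival.

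When such patients are pooled in one log-rank test, two things happen:

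- The hazard ratio that holds within each prognostic group is pulled towards 1, because high-risk patients leave the risk set early.
- If allocation was balanced on a prognostic factor, the usual variance is too large, so the test rejects slightly less often than its nominal level.

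Both reduce power. What is at stake is efficiency, not bias or false positives. The planned calculation has no margin (0.8004 against a target of 80%), and stratifying needs no extra patients or data.

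**Working it through.** **1. Reproduce the plan's figure.** Inputs from section 15 and the printed output: h1 = -ln(0.50)/5 = 0.1386; h2 = -ln(0.60)/5 = 0.1022; ratio 0.737; loss hazard w = 0.165; accrual 3 years; follow-up 5 years; 384 per arm.

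- P(event) = h/(h+w) × [1 − (e^(−5(h+w)) − e^(−8(h+w))) / (3(h+w))], giving 0.3909 and 0.3132.
- Events: 384 × 0.3909 = 150.1 and 384 × 0.3132 = 120.3, total 270.4 (plan: 150, 120, 270).
- Variances h²/P: 0.0492 and 0.0333 (plan: 0.049 and 0.033). SE = √((0.0492 + 0.0333)/384) = 0.01466.
- z = (0.1386 − 0.1022)/0.01466 = 2.488. One-sided power = Φ(2.488 − 1.645) = 0.800, which matches the plan. Two-sided at 0.05: Φ(2.488 − 1.960) = 0.701.

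So the plan's 0.8004 is a one-sided figure for a homogeneous population. The results below are one-sided unless marked, so that they compare with it.

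**2. Gain from stratifying by M status.** The M1 share (5% to 30%) and the M1:M0 hazard ratio k (2 to 8) are assumptions; the documents give neither. Simulated trials of 768 patients (2,500 to 4,000 per scenario) had overall control 5-year survival set to 50%, hazard ratio 0.737 within each M group and loss hazard 0.165.

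| k | Gain in power, in points, by M1 share |
|---|---|
| 2 | 0 to 2 at any share |
| 3 | about 2 at 5-10%; 3 to 5 at 15-30% |
| 4 | 6 to 7 at 15-20% (0.750 to 0.809; 0.740 to 0.808) |
| 5 | 3 at 5%; 6 at 10%; 7 to 9 at 15%; 11 to 12 at 20-30% |
| 8 | 4 at 5%; 9 at 10%; 13 at 15%; 18 to 20 at 20-30% |

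Monte Carlo error is about 1 point on each power. Two-sided gains are mostly larger.

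**3. Is planned power missed?** The plan's effect is for the whole population: 50% to 60%. A hazard ratio of 0.737 inside each stratum gives less than that. With 85% M0 at 57% and 15% M1 at 12% (k = ln 0.12/ln 0.57 = 3.8), control survival is 0.85 × 0.57 + 0.15 × 0.12 = 50.25%. D3 survival is 0.85 × 0.57^0.737 + 0.15 × 0.12^0.737 = 59.3%, a gain of 9.1 points. Restoring a 10-point gain needs a within-stratum ratio of 0.713. Power was simulated both ways (4,000 trials each):

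| Assumed mix (5-year control survival) | Ratio 0.737 within strata: plain / stratified | Overall gain 10 points: plain / stratified |
|---|---|---|
| 85% at 57%, 15% at 12% | 0.754 / 0.814 | 0.826 / 0.875 |
| 40% at 70%, 45% at 45%, 15% at 12% | 0.752 / 0.814 | 0.835 / 0.891 |
| 90% at 52%, 10% at 30% | 0.797 / 0.805 | 0.800 / 0.809 |

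The two-sided pairs for the first two mixes, at ratio 0.737, are 0.648 / 0.712 and 0.628 / 0.724. With the planned overall effect, the plain test keeps about 0.80 to 0.83 one-sided power. Stratifying adds about 1 to 6 points on top.

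**4. Size under no effect.** With allocation balanced on M (M1 share 10-20%, k 3 to 5, 4,000 trials each), the one-sided rejection rate at nominal 0.05 was 0.035 to 0.052 for the plain test and 0.046 to 0.056 for the stratified test.

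**5. Does it depend on M being a randomisation factor?** The power loss does not. With simple randomisation, 15% M1 and k = 5, power was 0.714 plain and 0.805 stratified.

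**The case against.** The strongest reply is that the article is merely silent. Strata for the primary test are often set in a statistical analysis plan, none is shown, and the restriction factors are deliberately held elsewhere. Some of this stands: the documents do not declare the test unstratified, and an unseen plan that names strata would settle the point. But section 15 does name the primary test, and for secondary comparisons it specifies the normality test, the choice between Fisher and Pearson tests and the imputation method. As written, it commits to a plain test where a better one is available. The strata can be tied to the randomisation factors by reference, without revealing the allocation list.

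A second reply is that the plain log-rank test is valid. That is right, and it limits the point to efficiency.

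A reader might infer three stronger things that the documents do not support:

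- **That the trial will miss its planned power.** With the overall effect held at 50% to 60%, the plain test reaches it. Powers in the 60s for the plain test come largely from testing two-sided, where even a homogeneous population has 0.701.
- **That a fixed loss, such as 7 to 15 points, can be stated.** That needs an M1 hazard about 4 or more times that of M0 and M1 at roughly 10-20% of patients or more. Only M1 patients with a documented plan for removing the metastases may enter (section 10.2), so a milder contrast is possible.
- **That analysis and randomisation are shown to conflict on M status.** The factors are undisclosed; M status may not be among them.

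**Conclusion.** The point holds as an improvement in efficiency. Section 15 names a log-rank test without strata for a prognostically mixed population whose randomisation is restricted. The test is valid, and mildly conservative if allocation is balanced on a strong prognostic factor.

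At the plan's loss hazard, the power given up is about 0 to 5 points if the M1 hazard is 2 to 3 times that of M0. It is about 4 to 9 points if the hazard is about 4 times with 15% M1, taking the runs together and allowing for simulation error. It reaches about 20 points (one-sided) only in extreme mixes, with k near 8 and 20-30% M1. These figures rest on assumed shares and survival, exponential survival within strata and a common hazard ratio across strata. Stratifying caused no material loss in any case run. No shortfall against the planned 0.8004 is shown.

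**What to change.** In section 15 (or the analysis plan, if it is to carry this detail):

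- Make the primary log-rank test stratified by the factors used to restrict randomisation and by M0/M1 and, if wanted, preoperative clinical stage.
- State a rule for pooling small strata, such as small centres, since very thin strata lose information.
- Report the hazard ratio from a Cox model stratified by the same factors.
- Keep the unstratified log-rank test as a sensitivity analysis.
- Fix the strata before outcome data are seen, so that they cannot be chosen on the result.
- Use preoperative stage only. Pathological N can depend on the extent of dissection, and so on the arm.

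The cost is a few lines of text. No extra patients are needed. M status and clinical stage are already established before randomisation, and the main centre holds the restriction factors.

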**Discussion:**

The results of this study will demonstrate whether extended lymph node dissection is superior to standard dissection in terms of oncological outcomes, and will also assess the impact of more extensive surgery on short‐term outcomes and quality of life.

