### Secondary aims of the study

6.2

To determine if there are any differences in disease‐free survival, short‐term outcomes after D2 and D3 lymph node dissections, assess quality of CME, lymph node yield and patients' quality of life.

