## Follow‐up

12

Schedule of necessary investigations and follow‐up visits is in *Appendix*
S3 (supporting information).

Visit day date deviation: 30 day visit +/‐ 2 days, other visits ‐ +/‐ week. Data on completed visits is transferred to eCRF in 5 working days. Quality of life is assessed via questionnaires filled in before surgery, on day 30, 3‐month visit, 1, 3 and 5‐year visits.

To minimize number of patients lost for follow‐up patients are able to provide results of their routine follow‐up investigations and get a consult of expert centre, which will facilitate patients' adherence to follow‐up.

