Prior to comparing of group mean values in case of quantitative data, a non‐parametrical criterion of Shapiro Wilks will be used to test the normality of distribution. In case of normal distribution Student's criterion for independent samples will be used (dependant samples for quality of life assessment). For data not distributed normally non‐parametric Mann–Whitney U criterion will be implied.

Lymph node metastases pattern will be assessed as calculation of frequency of affected nodes related to number of studied nodes in each group. Correlation analysis of association of size, T‐stage, localization of the tumour with affected groups of lymph nodes, frequency of metastases, tumour budding grade, lymphovascular and perineural tumour invasion. Spearman rank correlation coefficient will be used as the data may be distributed not normally and numeric data may be included. To assess correlation of quantitative data distributed normally Pearson correlation coefficient will be implied.

For the primary endpoint and disease free survival missing data will be handled according to the survival analysis nature – censoring of the patient with the date of last contact.

Missing data for the secondary endpoints will be dealt with by using multiple imputations with Markov chain Monte Carlo method (monotone method if the data shows a monotone pattern of missing values; otherwise, fully conditional specification).

Conclusion of superiority of D3 lymph node dissection will be made in case of statistical superiority of survival during the study of D3 group over D2.

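### The quality-of-life test rule lets a normality test decide whether change within patients or D2 versus D3 is tested

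*Protocol article*

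**What the plan says.** The relevant paragraph of section 15 (Sample size calculation and statistical analysis) opens with "Prior to comparing of group mean values in case of quantitative data", so it concerns the comparison of groups. A Shapiro–Wilk test comes first. If the data are normal, Student's "criterion for independent samples will be used (dependant samples for quality of life assessment". The next rule carries no such exception: "For data not distributed normally non‐parametric Mann–Whitney U criterion will be implied".

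Quality of life is one of the six secondary endpoints in section 7.3. The abstract describes it in its Methods as "quality of life in patients following D2 and D3 lymph node dissection", and its Discussion says that the results "will also assess the impact of more extensive surgery on short‐term outcomes and quality of life". Under section 12, "Quality of life is assessed via questionnaires filled in before surgery, on day 30", and then at 3 months and 1, 3 and 5 years. Section 7.1 allocates patients 1:1 to D2 or D3, and the synopsis gives 384 per arm.

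**The concern.** No D2 patient is matched to a D3 patient. The only pairing in these data is between visits of the same patient. A dependent-samples Student test on quality of life therefore tests whether scores changed over time. It neither estimates nor tests the difference between the operations, which is what the abstract's Discussion says the trial will assess.

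The non-normal route leads to Mann–Whitney U, which does compare two independent groups. The two routes thus answer different questions, and the Shapiro–Wilk result chooses between them. The quality-of-life instruments (EORTC QLQ-C30 and CR29) yield several scales at several visits. Some results could then be reported as change within patients and others as differences between arms, for no reason connected with the trial's aims.

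At stake is whether the quality-of-life results can be read consistently as a comparison of D3 with D2. That comparison is what would show any cost to patients of the larger dissection.

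**Working it through.** **Reading the two rules together.** Each intention that the authors might have had leaves one rule wrong.

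- If the aim is D2 versus D3, the normal branch is wrong, because a paired test does not compare the arms.
- If the aim is change within patients, the non-normal branch is wrong, because Mann–Whitney U is not a paired test.

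**Size of the effect.** The article gives no standard deviation, target difference or power for quality of life, so there is no stated figure to reproduce. The following is an illustration.

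Inputs: n = 384 per arm (synopsis). Assumed: SD 20 at each visit, correlation 0.5 between baseline and follow-up, normal scores, two-sided 5% tests.

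- SD of within-patient change = 20 × √(2 × (1 − 0.5)) = 20.
- Standard error of mean change in one arm = 20/√384 = 1.02.
- Standard error of the arm difference in follow-up scores = 20 × √(2/384) = 1.44.
- Power of the paired test for a 5-point fall: 5/1.02 = 4.90, and Φ(4.90 − 1.96) = 0.998. Significant in both arms: 0.998² ≈ 0.997.
- Power of the paired test for a 2-point fall: 2/1.02 = 1.96, and Φ(0) = 0.50.
- Power of the between-arm t test for a true 5-point difference: 5/1.44 = 3.46, and Φ(3.46 − 1.96) = 0.93.

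A simulation of 2,000 runs per scenario agrees:

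| Fall in each arm | Paired t significant in both arms | Paired t significant in exactly one arm | Independent t | Mann–Whitney U |
|---|---|---|---|---|
| 5 and 5 (no difference) | 99.7% | 0.3% | 4.9% | 4.9% |
| 5 and 10 (true difference 5) | 99.9% | 0.2% | 93.1% | 91.9% |
| 2 and 2 (no difference) | 23.6% | 50.9% | 5.2% | 4.9% |
| 0 and 0 (no difference) | 0.2% | 8.6% | 5.1% | 4.5% |

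The first two rows carry the argument. The paired results are practically the same whether or not the arms differ, whereas both between-arm tests separate the two situations.

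**Comparing within-arm p-values.** If the arms do not differ and each paired test has power p, the chance that exactly one arm is significant is 2p(1 − p).

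- p = 0.9: 2 × 0.9 × 0.1 = 18%.
- p = 0.5: 2 × 0.5 × 0.5 = 50%, the maximum.
- p = 0.998: 2 × 0.998 × 0.002 ≈ 0.4%.

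This matters only if someone takes significance in one arm and not the other as evidence of an arm difference.

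**The case against.** The strongest reply is that the parenthesis may simply cover change from baseline. Quality of life has a pre-operative score and five later visits, and a paired test is legitimate for describing such change. The article is condensed, and an analysis plan that is not shown may specify an arm comparison. That stands as far as missing detail goes: the lack of a longitudinal model here is no fault. It does not rescue the sentence, which states a specific rule in a paragraph on comparing groups and is at odds with the sentence after it.

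Stronger readings are tempting but not supported:

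- A reader might infer that the quality-of-life question would go unanswered. That does not follow, because non-normal scores go to Mann–Whitney U. Bounded questionnaire scores with up to 384 patients per arm may well fail Shapiro–Wilk, so the between-arm route could be the usual one. This too is an assumption, as no score distributions are given.
- A reader might take 50% as the false-positive rate. It is the worst case of 2p(1 − p), and nothing in the article proposes comparing within-arm p-values.
- A reader might cite section 6.2 as promising a test of quality-of-life differences. There, "To determine if there are any differences in" governs disease-free survival and short-term outcomes, while the later words are "assess quality of CME, lymph node yield and patients' quality of life". The comparative intent is clearer in the abstract.
- A reader might count the lack of baseline adjustment as an error. An unadjusted randomised comparison is valid; adjustment only gains precision.

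**Conclusion.** The rule is wrong as written and should be fixed. In the normal branch, quality of life is given a test that cannot address D2 versus D3. In the non-normal branch it is given one that can. The question answered therefore depends on a normality test.

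That conclusion follows from the wording and the parallel-arm design and does not rest on the simulation. The percentages do depend on the assumed SD of 20, correlation of 0.5 and normal scores.

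The weight is moderate. Quality of life is one of six secondary endpoints, and section 15 ties the superiority conclusion to survival alone. Randomisation, sample size and data collection are unaffected, so a correct comparison remains possible until the analysis is done.

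**What to change.** Delete the dependent-samples exception in section 15. State that QLQ-C30 and CR29 scores will be compared between D2 and D3 at each post-operative visit (day 30, 3 months, 1, 3 and 5 years), whatever the normality result.

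Preferably adjust for the pre-operative score, which is already collected. ANCOVA at each visit would do, or a repeated-measures mixed model with arm, visit and arm-by-visit terms. Report the difference between arms with its 95% confidence interval. Paired tests can stay, labelled as description of change within each arm and not as evidence about the difference between operations.

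The cost is a change of wording and slightly more analysis work. No new data are needed.
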